### Randomization

Clusters will be randomized all at once and their allocation will be carried out using stratified randomization by minimization. The minimization will use two important factors that can affect the statistical modeling and population homogeneity in the three arms. Indeed, minimization enables a better balance of the prognostic parameters between the different strategy groups than classical randomization, especially when the number of randomization units is small. The considered factors will be the type of local authority forming the cluster (independent cities only, cities which have been grouped for the present study because they were adjacent, or groups of cities, i.e. “*communautés de communes*” or “*communautés d’agglomérations*,” which are administratively grouped) and the size of the population, in order to have close distribution of local authority types and median size of population in the three arms.

The minimization parameters will be used to adjust statistical analyses of the primary and secondary outcomes. Randomization will be performed by an independent statistician who will not be involved in the further steps of the research.

### Blinding

The very nature of the intervention does not allow any form of blinding. However, participants living in the selected clusters will not be informed that their local authority is included in a randomized trial. Only those who use the StopBlues program will be asked to provide consent to have their data collected through the application or associated website (but this does not correspond to a consent to be included in the randomized trial). Moreover, the primary outcome will be assessed using administrative databases with a pre-specified algorithm. Therefore, although there is no blinding in the present trial, it is not at risk of performance bias or detection bias.

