However, e-health programs for suicide prevention should be associated with effective promotion strategies to ensure that people who could benefit from these programs are aware of them, as well as to help them identify reliable programs among those available online and encourage their use [19, 21]. In parallel with this targeted effect, such promotion campaigns may have ecological effects similar to those previously observed for other awareness campaigns [22–24], by decreasing the stigmatization associated with mental health issues in civil society, and changing the attitudes and norms associated with psychological distress in the adult general population. This would in turn facilitate help-seeking behaviors, leading to a decrease in the occurrence of psychological distress and suicidal ideations, and ultimately preventing suicidal acts. Suicide-prevention measures deployed in the community have been shown to be particularly effective in several studies [25–28], and previous research has involved cities or counties in the development of such measures [29, 30]. The additional involvement of health professionals, in particular general practitioners (GPs), in promotion campaigns for suicide prevention carried out at the local level could also be beneficial. Indeed, even if people with mental disorders prefer not to seek formal professional help [22], GPs are the health specialists whom people suffering from psychological distress or at risk of suicide most easily turn to, even if not always addressing these topics directly. Among people who committed suicide, 20% did so within 1 day of a visit to their GP [31]. Involving local authorities as well as GPs in promoting suicide-prevention actions through dedicated interventions could, therefore, have complementary benefits, provided that they address the potential lack of sufficient skills, as well as of technical, financial and human resources at their level. However, to the best of our knowledge, no study has involved a large number of local actors in the promotion of an evidence-based e-health tool for suicide prevention, although the development of promotion measures for e-health programs has been advocated by previous work [19, 21].

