#### Secondary objectives

The secondary objectives will be measured both at the cluster level (geographical area sharing a common authority) and among users of the StopBlues program.

Secondary objectives considered at the cluster level are as follows:
To assess the cost-effectiveness and to run a budgetary impact analysis of the intervention

Secondary objectives measured among users of the StopBlues program are as follows:
2.To assess the effectiveness of the intervention in terms of the intensity of the utilization of the program3.To assess the effectiveness of the intervention for help-seeking behaviors and participation in supportive activities (any activity that a user finds beneficial for their mental health)4.To assess the effectiveness of the intervention for the evolution of the level of psychological impairment

It should be noted that an additional form of promotion (more sustained promotion by local authorities, described below) will be implemented after 12 months in the control group and evaluated using the same primary outcome measure. In parallel, the long-term effectiveness of the two main types of local promotion (with or without a passive involvement of GPs through their waiting room) will also be assessed.

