### Outcomes

#### Primary outcome measure

The primary outcome measure will be the number of suicidal acts (both death by suicides and suicide attempts) during the 12 months after the start of the intervention. The number of deaths by suicide will be obtained from the Epidemiology Center for Medical Causes of Death (“*Centre d’épidémiologie sur les causes médicales de décès”*, CépiDc) while the number of suicide attempts will be approximated by the number of suicide attempts in contact with the healthcare system (other than primary care only). To estimate the number of suicide attempts seen in acute care, we will use the exhaustive French National Hospital Discharge Database (“*Programme de médicalisation des systèmes d’information en médecine, chirurgie, obstétrique*,*”* PMSI-MCO) [40]. To estimate the number of suicide attempts seen in emergency care, we will use the *Oscour* database which records visits to emergency departments [41]. Participants from clusters included in the study will be identified through their zip code of residence.

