#### Ethical considerations

This trial was granted ethical approval by the relevant ethics committee (see the “Declarations” section below). It should be noted that participants are not informed that they are included in a randomized trial. Randomization is carried out at the cluster level (geographical areas). There are no opt-out options for people living in geographical areas allocated to one of the two experimental groups, and there is no direct relationship with participants to collect data for the primary outcome. Absence of information and consent to be included in the trial is, therefore, in agreement with the Ottawa Statement on ethical issues for cluster-randomized trials [62]. This was also positively assessed by the relevant ethics committee. In addition, the risk to users of the StopBlues program was evaluated as minimal due to a number of specific features of the program (emergency “get help now” button, safety plan, locator of nearby helps, push-up notifications reminding users to get help, information on prevention regularly updated, etc.). In particular, if someone expressed suicidal ideation while using the program, they would straight away be directed to a call either to general health emergency services (“get help now” button) or to their personal emergency contacts (professionals or relatives) if they filled in the safety plan. All this explains that no data monitoring committee was created for this study and that no detailed stopping guidelines for the trial were enacted. Nevertheless, if an increase in the number of suicidal acts was to be found in the participating local authorities during the first round of analysis of data, the decision to stop the trial could be taken in consultation with funders and health authorities. They will also be involved in the decision to continue the intervention after the trial based on its results.

All users of the StopBlues program will provide written informed consent before their data is collected for research purpose. They will indeed have to sign a consent form for participation in the intervention and will be able to withdraw from the research whenever they want. Their data will be stored on a secure server and any identifying information necessary for the access to the program (email address) will be encrypted through a unique user identifier. Data files used for linkage will be stored separately from raw research data.

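### The protocol rules out detection bias, but it counts attempts only through hospital or emergency contact, and the promotion is meant to raise help-seeking, so the share of attempts counted may differ by arm

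*Protocol article*

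**What the plan says.** The Blinding section accepts that nobody can be blinded, but states that "although there is no blinding in the present trial, it is not at risk of performance bias or detection bias". It offers two reasons: residents are not told that their area is in a randomized trial, and "the primary outcome will be assessed using administrative databases with a pre-specified algorithm".

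The primary outcome is "the number of suicidal acts (both death by suicides and suicide attempts) during the 12 months after the start of the intervention". Deaths come from the national cause-of-death register (CépiDc). The number of attempts "will be approximated by the number of suicide attempts in contact with the healthcare system (other than primary care only"), taken from hospital discharges (PMSI-MCO) and emergency department visits (Oscour).

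Several sections make help-seeking part of how the intervention should work:

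- The Background expects the campaign to reduce stigma and says: "This would in turn facilitate help-seeking behaviors, leading to a decrease in the occurrence of psychological distress and suicidal ideations". It also lists a locator of nearby help and an emergency button among the program's features.
- Under Secondary objectives, one aim is: "To assess the effectiveness of the intervention for help-seeking behaviors and participation in supportive activities".
- Under Ethical considerations, of users who express suicidal ideation: "they would straight away be directed to a call either to general health emergency services", or to their personal emergency contacts if they have completed a safety plan.

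Statistical considerations plans a Poisson regression adjusted for the count in the 12 months before launch, and compares suicides and attempts separately as well as together.

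**The concern.** The two reasons given deal with who knows the allocation and how records are classified. Neither deals with whether an attempt produces a record at all. An attempt that never reaches a hospital or emergency department is invisible to any coding algorithm, however objective. If promotion changes what people do after an attempt, the counted fraction shifts in the promoted arms only.

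The planned effect is small, so a modest shift could take away much of the observed benefit and power. The same count is mentioned under Ethical considerations, where an observed increase in suicidal acts could lead to a decision to stop the trial.

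**Working it through.** **Inputs**

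- Control rate 0.215%, experimental rate 0.190%, power 80%, type I error 2.5%, 1,229,350 participants, 11 clusters per arm, mean cluster size 138,172, ICC about 10⁻⁵ (Sample size and power).
- Suicide deaths 13.8 per 100,000 inhabitants (Background). This is a national figure, assumed here to apply to the trial areas.
- Relative rise *a* in the share of attempts reaching hospital or emergency care, promoted against control. The document gives no value, so *a* is an assumption, shown as a range.

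**1. The plan's own figure.** Two proportions, pooled variance, two-sided 2.5%, 80% power: 614,678 per arm, 1,229,356 in total, against the stated 1,229,350. It reproduces. (The article does not state sidedness; one-sided 2.5% gives 1,015,154.)

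**2. Design effect.** 11 × 138,172 = 1,519,892 per arm. 1,519,892 / 614,675 = 2.47. The implied ICC is (2.4727 − 1) / 138,171 = 1.07 × 10⁻⁵, in line with the stated value. The power figures below use this design effect.

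**3. Share of events that depends on care contact.** Deaths: *w* = 13.8 / 215 = 0.064. Attempts: 1 − *w* = 0.936, about 94%. This is the share of events that are attempts, not the share whose counting could change.

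**4. Observed rate ratio when the planned effect is true.** True RR = 0.190 / 0.215 = 0.8837. Then observed RR = 0.8837 × [*w* + (1 − *w*)(1 + *a*)].

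| Assumed rise *a* | Observed RR | Power |
|---|---|---|
| 0% | 0.884 | 80% |
| 2% | 0.900 | 65% |
| 5% | 0.925 | 39% |
| 10% | 0.966 | 9% |
| 14% | 0.9995 | effect cancelled |

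With the ICC at exactly 10⁻⁵ (design effect 2.38), power is 82%, 67%, 41% and 9% for the first four rows.

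**5. Exact cancelling point.** 1 + *a* = (1 / 0.8837 − 0.0642) / 0.9358 = 1.141.

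**6. Feasibility.** Let *s* be the control-arm share of attempts that already reach care (not in the document). The share in a promoted arm cannot exceed 1, so 1 + *a* ≤ 1/*s*. Full cancellation therefore needs *s* below 1 / 1.141 = 0.877, about 88%. More generally, *a* = *x*(1 − *s*)/*s*, where *x* is the share of otherwise uncounted attempts across the whole cluster that promotion turns into counted ones:

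| Assumed *s* | *x* for *a* = 2% | 5% | 10% | 14% |
|---|---|---|---|---|
| 0.5 | 2% | 5% | 10% | 14% |
| 0.8 | 8% | 20% | 40% | 56% |

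**7. No true effect.** With *a* = 10%, observed RR = 0.0642 + 0.9358 × 1.10 = 1.094. The chance of a significant apparent increase is about 54%.

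**8. What the planned analyses can do.** Baseline adjustment uses counts from before launch, so it cannot absorb a shift that begins after launch in the promoted arms. Deaths escape this route, but 1,519,892 × 0.000138 ≈ 210 deaths in control against 210 × 0.8837 ≈ 185 gives power of about 16% ignoring clustering, or about 7% if the same ICC of 10⁻⁵ is assumed. The separate attempts count carries the same possible bias as the composite.

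**The case against.** The mechanism is less direct than it first appears. The Background places help-seeking before the attempt, where it should prevent acts. The emergency routing concerns expressed ideation, also offers personal contacts, and a call about ideation is not a counted attempt. The help-seeking outcome includes lay help, which could even draw someone away from emergency care. The program is available in every arm, so only the extra effect of promotion across the whole cluster matters. The feasibility table shows that, if most attempts already reach care, the larger rises need a large behavioral change. The protocol also openly calls the attempt count an approximation and analyzes deaths separately. All of this stands. It makes the size uncertain and the direction plausible rather than proven, but it does not support a categorical statement that the risk is absent.

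Three stronger readings are tempting and should be resisted:

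- A reader might infer that the intensified arm moves attempts across the primary-care boundary through GPs. The intervention section describes only leaflets and posters in waiting rooms, so nothing supports this.
- A reader might infer that an increase in recorded acts stops the trial automatically. The text describes a discretionary decision taken in consultation, with no detailed guidelines.
- A reader might infer that an increase could safely be dismissed as better ascertainment. That would discard a possible harm signal in a trial without a data monitoring committee.

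**Conclusion.** The claim of no detection bias cannot stand beside the protocol's own definition of a counted attempt and its stated aim of increasing help-seeking. The point concerns detection bias only; the performance-bias half of the sentence is not examined here. About 94% of expected events pass through the care-contact filter, assuming the national death rate applies to the trial areas.

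The document gives neither the rise in care contact nor the share of attempts already reaching care, so the calculation shows sensitivity and does not predict a bias. On the plan's own rates, an assumed 5% rise roughly halves power. Complete masking of the planned effect needs a rise of about 14%, and so a control-arm share below about 88%. It would go too far to say that the trial will hide a benefit or show false harm.

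**What to change.** - Withdraw the statement of no risk as far as it concerns detection bias. State that ascertainment of attempts may differ by arm, and that the likely direction is against the intervention.
- Keep the composite as the primary outcome.
- Pre-specify supportive results by source and arm: CépiDc deaths, PMSI-MCO admissions and Oscour emergency visits, with visits not followed by admission shown separately where the data allow. Note that admissions also depend on contact with care.
- Add a sensitivity analysis that re-expresses the composite rate ratio over a stated range of ascertainment ratios, including the value at which the conclusion changes.
- Cross-refer to this limitation where Ethical considerations discusses an observed increase in suicidal acts, without declaring in advance that an increase will not be read as harm.

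The cost is wording and a few extra models on data already to be extracted. The supportive outcomes have fewer events and will be less precise. Separating emergency-only visits may need discharge status or linkage, which the article does not describe for Oscour.

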### Intervention to be evaluated

The intervention evaluated corresponds to the tailored local promotion of the StopBlues program. Its description below complies with the Template for Intervention Description and Replication (TIDieR) Checklist for intervention description [38].

The StopBlues program will be promoted by the French local authorities participating in the trial. A basic communication toolkit, including a promotion guide, posters, leaflets and key communications messages, will be provided to each local authority at the beginning of the intervention. In addition, a contact person from the municipal staff already involved in health prevention will be appointed in each local authority. They will be in charge of coordinating the promotion of the StopBlues program at the local level and will participate in a day-long training session prior to the beginning of the promotion campaign. Local authorities will then be in charge of promoting the program by choosing their usual municipal communication medium (local newspapers, bulletins and billboards, posters in local shops and bus stops, etc.), by involving local actors of their choice and by developing additional promotion tools if they wish. They will, therefore, be able to develop a tailored intervention adapted to their local context.

Additional promotion of the StopBlues program (intensified promotion) will be carried out in several local authorities by the additional involvement of local GPs. As GPs’ workload is significant in France, due to the fact that they have been put at the heart of care coordination [39], a passive involvement of GPs in the promotion of the StopBlues program was designed. They will receive communication tools on the StopBlues program, such as leaflets or posters, to put in their waiting rooms in order to inform patients and their relatives about the existence of the program.

Finally, the local authorities of the control group will be offered a more sustained promotion at 12 months, which is not part of the main intervention but will also be evaluated during the trial. This promotion will consist of the same promotion as in the basic promotion group to which will be added regular support from the research team with stronger contacts and technical and financial resources for local authorities to implement the promotion and print the tools (flyers, posters, etc.). The inclusion of GPs in this promotion process will be left to local authorities’ discretion.

### Outcomes

#### Primary outcome measure

The primary outcome measure will be the number of suicidal acts (both death by suicides and suicide attempts) during the 12 months after the start of the intervention. The number of deaths by suicide will be obtained from the Epidemiology Center for Medical Causes of Death (“*Centre d’épidémiologie sur les causes médicales de décès”*, CépiDc) while the number of suicide attempts will be approximated by the number of suicide attempts in contact with the healthcare system (other than primary care only). To estimate the number of suicide attempts seen in acute care, we will use the exhaustive French National Hospital Discharge Database (“*Programme de médicalisation des systèmes d’information en médecine, chirurgie, obstétrique*,*”* PMSI-MCO) [40]. To estimate the number of suicide attempts seen in emergency care, we will use the *Oscour* database which records visits to emergency departments [41]. Participants from clusters included in the study will be identified through their zip code of residence.

#### Secondary outcome measures

##### Cost-effectiveness and budgetary impact analysis

The cost-effectiveness and budget impact of the intervention will be assessed using a societal perspective. The budget impact analysis will be carried out at 12 and 24 months while the cost-effectiveness analysis will be evaluated over the entire user’s lifetime.

Costs linked to the implementation of the intervention will be measured at 12 months and at the end of the intervention. They will include fixed costs resulting from the creation of the promotion toolkit for the StopBlues program. They will also include semi-fixed costs, linked to potential specific communication strategies developed by the different local authorities for the implementation of a tailored intervention, and to the human resource costs of involving municipal staff. Costs of suicidal acts will be estimated by considering direct costs for the healthcare system as well as indirect costs for individuals attempting suicide and their relatives.

Moreover, we will use the 12-item Short Form health survey (SF-12) [42] among users of the StopBlues program to obtain a generic measure of perceived health-related quality of life which can then be used to estimate a preference-based measure of health for economic evaluations [43]. This has been previously validated in French [44].

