### Sample size and power

The number of clusters was fixed by the identification of 34 clusters that agreed to be involved in the trial. The proportion of inhabitants who died from suicide or who made suicide attempts over a 12-month period was estimated to be 0.215% (personal data). We used an expected rate of 0.190% in the experimental group, which represents a reduction of 11.6%, slightly higher than the 10% global target supported by WHO for interventions on suicide [10]. In a two-arm, individually randomized trial, this would lead to a required number of participants of 1,229,350 to achieve a power of 80% with a Type I error rate of 2.5%. Type I error is set at 2.5% because two experimental groups are compared to the control group. Clustering also has to be taken into account. As the number of voluntary clusters was fixed, we calculated what the intraclass correlation coefficient (ICC) would be in order to achieve a power of 80% with our pre-specified number of clusters. Although we acknowledge that such an approach is not classical, it enables us to take into account feasibility reasons. Our mean cluster size equals 138,172 inhabitants and, therefore, randomizing 11 clusters in each arm allows for achieving 80% power if the ICC is around 10^−5^. Although this is a very low ICC, one has to keep in mind that clusters are geographical areas and ICCs are known to be lower in large clusters as compared to small ones. Moreover, ICC is known to depend on prevalence [37], with small ICC values for prevalence close to 0 or 1, and we expect very low rates (about 0.2%). As a consequence, we considered that a 10^−5^ ICC value would be appropriate in our trial.

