#### Dissemination plan

Findings from the research will be published in aggregated form at the local authority level (no information on individual users of the StopBlues program will ever be provided). Given the broad scope of research objectives for this trial, the dissemination plan for this study includes several publications reporting on preliminary and secondary outcomes. Authorship will be based on actual contributions to the research work. Scientific publications will be complemented by communications aimed at policy-makers in order to ensure the continuation of the intervention, after termination of its funding in the framework of the research project, if results prove satisfactory.

The trial outcomes will be reported in line with the Consolidated Standards of Reporting Trials (CONSORT) guidelines for cluster-randomized trials [63, 64]. An anonymized dataset (therefore, not requiring additional consent) will also be made available by the authors within 3 years of the final collection of data. This dataset will be made available to other researchers for the development of further studies, upon submission of a research protocol to our research consortium and after obtaining adequate ethical approvals.

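### A societal perspective is set for the budget impact analysis as well as for cost-effectiveness, so the budget result as written does not show what any payer would spend or save

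*Protocol article*

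**What the plan says.** Under Secondary objectives, the protocol article lists the economic work as two tasks: "To assess the cost-effectiveness and to run a budgetary impact analysis of the intervention".

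Under Cost-effectiveness and budgetary impact analysis, it sets one perspective for both: "The cost-effectiveness and budget impact of the intervention will be assessed using a societal perspective". The next sentence separates them by horizon only: "The budget impact analysis will be carried out at 12 and 24 months while the cost-effectiveness analysis will be evaluated over the entire user’s lifetime".

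One cost list then serves both analyses:

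- fixed costs of creating the promotion toolkit;
- semi-fixed costs of local promotion, described as "linked to potential specific communication strategies developed by the different local authorities for the implementation of a tailored intervention, and to the human resource costs", the latter for municipal personnel;
- costs of suicidal acts, made up of direct healthcare costs "as well as indirect costs for individuals attempting suicide and their relatives".

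The section does not say which components enter which analysis. No budget holder is named for the budget impact analysis.

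Under Dissemination plan, publications are to be complemented by "communications aimed at policy-makers in order to ensure the continuation of the intervention" once research funding ends, provided the results are satisfactory. Under Ethical considerations, funders and health authorities take part in deciding whether the intervention continues after the trial.

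**The concern.** The two analyses answer different questions. Cost-effectiveness asks whether the health gain is worth the resources used, whoever provides them, so a societal perspective is a legitimate choice. Budget impact asks what an identified body will spend or save over a short period. It needs a budget, and only flows into or out of that budget count.

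A societal perspective on budget impact blurs this in two ways. Losses carried by individuals and relatives, once averted, are set against promotion spending although no public account records them. In addition, the bodies that pay and the bodies that save are merged: communication and municipal staff costs arise at local authorities, while avoided hospital and emergency care is a saving to the healthcare system.

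At stake is the usefulness of a named secondary objective. If the budget figure is used when continuation is discussed after the grant ends, the bodies asked to pay could not read their own position from it.

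**Working it through.** **1. Text side by side.** The perspective sentence names both analyses. The horizon sentence shows that the authors distinguished the two where they wanted to. The cost list is given once, includes indirect costs, and carries no exclusion for budget impact. The plain reading is that all listed components enter both analyses.

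**2. Inputs for the size** (Sample size and power):

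- control proportion over 12 months: it "was estimated to be 0.215% (personal data");
- expected proportion under promotion: 0.190%;
- mean cluster size 138,172; 11 clusters per arm.

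The plan's own figure was checked first. Two proportions of 0.00215 and 0.00190, 80% power and a two-sided 2.5% error rate give 614,678 per arm, or 1,229,356 in total. The article states 1,229,350, so the rates reproduce its calculation. The relative reduction is 0.00025 / 0.00215 = 11.6%, as stated.

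**3. Acts averted if the design effect occurs.**

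- Per cluster: 138,172 × (0.00215 − 0.00190) = 34.5
- Inhabitants per arm: 11 × 138,172 = 1,519,892
- Per promotion arm per year: A = 1,519,892 × 0.00025 = 380

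**4. Who bears what.** Let T be the toolkit cost, L the local authorities' cost, and d the direct healthcare cost per act. Let i be the indirect cost per act, split as i = b + u, where some payer bears b and no payer bears u. None of these is given in the document.

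| Body | Net cost at A acts averted |
|---|---|
| Body paying for the toolkit | T |
| Local authorities | L |
| Healthcare payer | −A·d |
| Any payer bearing part of the indirect cost | −A·b |
| Individuals and relatives | −A·u |
| Societal total | T + L − A·(d + b + u) |

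Two results follow.

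- *Indirect costs.* The societal total shows a saving larger than that of all payers together by A·u, or about 380·u per promotion arm per year at the design effect. At A = 0 this term is zero. If acts increase, A is negative and the term makes the budget result look worse than it is for payers.
- *Pooling.* Even with u = 0, the total T + L − A·(d + b) equals no single body's position. A local authority facing +L would see its cost offset by −A·d, which accrues to someone else.

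**5. Scale, under assumed values only.** If u were 1,000, 5,000 or 20,000 euros per act, then 380·u would be about 0.38, 1.90 or 7.60 million euros per promotion arm per year. These unit costs are assumptions chosen to show a range; they do not come from the document and are not estimates.

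**The case against.** The strongest reply has four parts.

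- *A condensed article.* It may have put the perspective of two analyses into one sentence and left the allocation of costs to payers to an economic analysis plan that is not shown. It nowhere says, line by line, that indirect costs enter the budget impact result. This stands in part. An unnamed payer alone would not be a finding in an article, and the entry of indirect costs is inferred from the shared perspective and the single list. But the perspective itself is stated, for both analyses. A fuller document could only repeat that statement or contradict it.
- *Convention.* The narrower perspective for budget impact comes from general practice, not from this document, and a broad view has some appeal where several bodies carry costs. Several bodies carrying costs is, however, the reason to show each one separately.
- *Indirect costs and public payers.* Some could fall on a public payer, income replacement for instance (an assumption). This stands: only the part that no payer bears is misplaced, which is why the working splits i.
- *Link to decisions.* The Dissemination plan does not mention budget impact and makes continuation depend on satisfactory results. This also stands. The document does not show that policy-makers would be given this particular figure.

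A reader might go further and infer that the affordability result is overstated outright, or by a fixed multiple such as 1 + i/d. The document supports neither. Overstatement requires that acts fall, and no unit cost or promotion cost is given from which a multiple or a change of sign could be derived.

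**Conclusion.** The point holds in limited form. The document assigns a societal perspective to the budget impact analysis and gives no exclusion for costs borne by individuals and relatives. Followed as written, the 12- and 24-month result mixes costs of several public bodies with costs that fall on none, so it does not answer a budget question. The mixing of payers does not depend on the trial's outcome.

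The overstatement of payer savings is conditional. At the design effect of 0.215% against 0.190%, with 11 clusters of 138,172 per arm, it equals about 380 acts per promotion arm per year times the indirect cost per act that no payer bears. It is zero without an effect and reversed if acts increase. Its amount in euros cannot be obtained from the document.

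The primary analysis and the non-economic outcomes are unaffected. The sentence should be amended before the economic analysis is done.

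**What to change.** Replace the shared perspective sentence with two statements, for example:

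*Cost-effectiveness will be assessed from a societal perspective. Budget impact will be estimated separately for each body that bears costs (the healthcare payer, the local authorities, and the funder or other body that pays for the toolkit), counting only expenditures and savings falling on that body at 12 and 24 months. Indirect costs to individuals and relatives will be reported separately, outside the budget impact total.*

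The toolkit payer should be listed explicitly. A list limited to the healthcare payer and local authorities could drop toolkit costs borne by the research team or a funder and so flatter the result. If part of the indirect costs falls on a public payer, that part belongs in that payer's account.

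The cost is some extra work. Table 2 lists the promotion costs as data collected by the research team and local authorities, but the costs of suicidal acts are still to be estimated, and those estimates must be allocated to payers. The resulting budget figure may be less favourable. The conduct of the trial and its outcome measures do not change.
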